## Description of investigational products

Irinotecan – 360mg/m^2^: This investigational drug will be procured in a syringe by the hospital pharmacy for a one-time administration. It will be injected into the HIPEC perfusate circulating in the hyperthermic pump via the injection site. It will be injected together with oxaliplatin that is a non-investigational drug that all patients will receive irrespective of arm.

5-fluorouracil – Maximum tolerated dose of 1-day EPIC to be determined: This investigational drug dose will be divided into two separate syringes. It will be injected through two of the remaining passive abdominal drains. After injection, the drain will be cleared from chemotherapy with a saline solution injection. The drains will be clamped. The estimated peritoneal clearance is 8-10 hours. The clamps need to be closed 16 hours. They are then opened for drainage of fluid collections to occur according to our clinical routine for abdominal drains in HIPEC.

## Packaging and labelling of investigational products

5-Fluorouracil is found in the dose 50mg/ml in 20 ml or 100ml glass injection bottles that are packaged in a carton. Even though we advocate the use of Fluorouracil Accord, Fluorouracil Tevo may also be used. They have the exact same dosage, glass bottle sizes, and packaging type.

Irinotecan is provided by three companies in Sweden: Accord, Actavis, and Fresenius Kabi. All of the companies use the same dosage of 20mg/ml. The have different sizes of injection bottles packaged in cartons. All three companies may be used depending on what the local hospital pharmacy has in storage. Since there is no blinding in the study and the drugs are post-market drugs, the investigational drugs of irinotecan and 5-fluorouracil for intraperitoneal administration will be labelled as is with irinotecan and 5-FU and with respective doses on the syringes.

## Storage and handling

Both drugs are actively used every week in the medical oncology outpatient clinics in all four participating centers in routine oncology treatment. Thus, each center hospital has a constant turnover of the investigational medicinal product (IMPs) fluorouracil and irinotecan. Due to the common use of these drugs, there is little need for specific IMP drug oversight. Each pharmacy will store, handle, dilute and prepare the drugs according to the specifics as described in the published marketing drug IMP brochure (see FASS.se).

## RandomiZation and blinding

Patient randomization will be integrated into the HIPEC registry and will be performed intraoperatively after abdominal exploration and after a CC 0 result is deemed achievable. For patients with isolated peritoneal metastases, there will be center stratification and PCI stratification (PCI 1-10 vs 11+). For patients with combined liver and peritoneal metastases, there will be only PCI stratification (PCI 1-10 vs 11+). Multivariable regression will be used in the results section in order to account for skewed differences in baseline differences. See the planned statistical analyses (13.2).

There is no blinding involved in this trial. This is mainly due to the fact that one arm will need to receive G-CSF treatment postoperatively; and thus, the treating physician needs to know which arm the patient is allocated to. The primary endpoint is recurrence free survival which is determined by radiologists on a CT scan. The radiologists will not be privy to the treatment allocation. Thus, there is a blinding of primary endpoint evaluation.

## Concomitant therapy

All necessary medical treatment needed to manage possible surgical or HIPEC/EPIC related complications are permitted. Likewise, all medications that the patient is currently taking may be administered as usual unless a very specific drug interaction needs review by a site investigator. In which case, depending on the medication, it may be temporarily discontinued in the postoperative period. Concomitant medication administered the day before and the day of surgery is registered in an eCRF.

Adjuvant systemic chemotherapy is administered according to each center’s clinical routine and will be registered in the HIPEC registry.

The patient may not join another adjuvant treatment trial study prior to recurrence without the consent of the study committee. A judgement concerning the effect on this current study will need to be performed before allowing inclusion into a concomitant study, which by principle will generally not be allowed unless it is systematically applied to all included patients and a renewed sample size calculation has been performed.

## Accountability of investigational products

The study requires a less rigorous accountability as the use of both drugs is commonplace in routine oncological treatment of colorectal cancer. The drug is ordered from the operating room the same morning that it is administered. It is delivered approximately 1-2 hours after a prescription is sent to the pharmacy from the operating room. If the products are not administered as planned due to an unforeseen event during surgery, they will be returned to the pharmacy for destruction and logged as not administered. This will be noted in the registry treatment follow-up.

## rOLE AND RESPONSIBILITIES OF TREATING PHYSICIANs

The investigators and co-investigators include almost all HIPEC treating physicians in Sweden as this is a small subspecialty. Each site investigator and co-investigator is responsible for all eCRF data input and study related visits. GCP training is required of all investigators. GCP training can be offered to those needing the training. Financial costs for GCP training may come from the study budget, if needed. They may enlist the help of a GCP trained research nurse for study assistance. Each site may delegate responsibility of study visits to other physicians in the same department by a signed delegation ensuring GCP training as well.

# ASSESSMENT OF EFFICACY

The primary endpoint in the efficacy trial is RFS after 12 months. Data from the one-year postoperative clinical follow-up that is registered in the HIPEC registry will be retrieved. Besides the site of relapse, also the date of recurrence is retrieved. It is defined as the date of the radiological examination that identifies the recurrence. Crude overall survival will also be assessed at the end of the trial follow-up as a secondary endpoint for the trial. The HIPEC registry is automatically connected with the Swedish death registry and therefore the overall survival follow-up is completely automatic as to the date of death. However, cause of death will also be retrieved from the cause of death registry in order to perform exploratory analyses of cancer specific survival. Likewise, quality-of-life will be retrieved from the HIPEC registry as well.

## Clinical and laboratory assessments

### Timing and method of the assessment

The dose titration is assessed continuously as each dose level is completed. All morbidity data is retrieved from the HIPEC registry.

Patient follow-up:

Mandatory

- Abdominal and thoracic CT scan at baseline before surgery and 12 months postoperatively.
- Treatment administered (CRS+HIPEC+EPIC variables)
- Morbidity to be submitted within 30 days from treatment administration. SAE and SUSAR are to be reported immediately (a separate section will make this possible in the HIPEC registry)
- Overall survival follow-up at
- 5 years from the HIPEC registry

Clinical routine

- The following follow-up is standard in Sweden after CRS+HIPEC: CT scan and tumor markers every 6 months for 2 years and then annually for another 3 years. Since all these follow-ups are not included in the HIPEC registry, we will not include them in the schedule of investigational events.
- EORTC QLQ-C30, CR29, and STO22 questionnaires filled out at baseline, 3, 12 and 36 months after surgery using the established QoL database. All patients are included in the quality-of-life registry as part of the clinical quality assurance follow-up, unless they specifically have requested not to be included.

Optional: Sending intraoperative tumor tissue to Uppsala for chemoresistance testing within 48 hours. Tissue is discarded right after testing. No biobanking will occur.

#### CT scan

A relatively recent CT scan within 6 weeks of the treatment administration is needed. Likewise, a radiologist evaluation of the 12-month CT scan needs to be registered in the HIPEC registry. If a recurrence has occurred prior to 12 months, the earlier date for the CT scan where the recurrence was noted is to be used.

#### Tumour markers

Carcinoembryonic antigen (CEA), Cancer antigen 19-9 (CA 19-9), Cancer antigen 125 (CA 125).

#### Health-related quality-of-life assessment

EORTC QLQ-C30 and CR29 and STO22 forms will be used to evaluate quality-of-life [10]. These forms will be sent out at baseline, 3, 12, and 36 months. The primary outcome is the comparison of questions 29 and 30 from the QLQ-C30 at 12 months rated 1-7, where 1 is very poor and 7 is excellent.

QLQ-C30 questions for QoL assessment:

29. How would you rate your overall health during the past week?

30. How would you rate your overall quality of life during the past week?

#### Translational study

To assess chemotherapy resistance and their capacity to predict treatment outcome, tumor tissue will be sent during surgery at Uppsala University Hospital, Uppsala, Sweden, to the chemotherapy resistance testing lab at the hospital. This part of the study is optional for the other three HIPEC centres in Sweden. Using the IC_50_ value attained from the test results [11], a Cox proportional hazards model will be implemented to evaluate whether the resistant oxaliplatin/irinotecan/5-FU values (top 1/3 of the whole study cohort’s IC_50_ values vs bottom 2/3) lead to poor survival outcome, both overall survival and recurrence-free survival. Patients having received at least one sensitive drug during treatment will be compared to the patients having received only resistant drugs.

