| Number of subjects (planned):  Dose escalation study: min 15 and max 30 patients - Number of patients is based on toxicity observed.  Efficacy study: 326 patients. Interim analysis is done after 140 patients are included | | |
| Diagnosis:  Colorectal cancer | | |
| Inclusion criteria:   1. Provision of written informed consent prior to any study specific procedures. 2. ECOG Performance Status Score 0,1 or 2 alternatively Karnofsky 60-100 3. Adequate kidney, liver, bone marrow function according to laboratory tests 4. For females of childbearing potential, a negative pregnancy test must be documented 5. ≥ 18 years old and <75 years old 6. Colorectal cancer with peritoneal metastases +/- liver metastases (maximum 3) 7. All patients deemed eligible for CRS and HIPEC according to clinical routine management during a HIPEC multidisciplinary board at each respective hospital can be included. | | |
| Exclusion criteria:   1. Previous severe toxicity/allergic reactions to systemic chemotherapy agents oxaliplatin or irinotecan or 5-fluorouracil 2. Unable to tolerate intensified HIPEC treatment due to comorbidity 3. Metastasis other than peritoneum or liver 4. Complex liver-perenchymal sparing surgery or hemihepatectomy procedures are to be excluded. 5. Previous CRS or HIPEC 6. Pregnant or lactating (nursing) women 7. Active infections requiring antibiotics 8. Active liver disease with positive serology for active hepatitis B, C, or known HIV 9. Concurrent administration of any cancer therapy other than planned study treatment within 4 weeks prior to and up to 4 weeks after study treatment 10. Incomplete cytoreduction defined as completeness of cytoreduction score 1-3 11. Histopathology of other origin than colorectal cancer | | |
| Investigational product, dosage and mode of administration:  Injection of irinotecan 360 mg/m^2^ and 5-fluorouracil 24-hr EPIC 250-850 mg/m^2^ in combination with Oxaliplatin 360 mg/m^2^ and an intraoperational IV of 5-fluorouracil bolus 400 mg/m^2^ with calcium folinate 60mg/m^2^.  The EPIC treatment is given after the abdomen is completely sutured in the operating theatre. The dose will be divided equally into 2 injections á 200ml each through two abdominal drains. | | |
| Duration of treatment:  24 hours | | |
| Active control, dosage and mode of administration:  Injection of oxaliplatin 460 mg/m^2^ and an intraoperational IV of 5-fluorouracil 400 mg/m^2^, and calcium folinate 60 mg/m^2^ | | |

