## Justification of Study design

The reason for going from a phase I to III combined approach is that the triple drug treatment (oxaliplatin, irinotecan, and 5-FU) has already been used in the medical oncology clinic as a routine clinical treatment for many years with a well-known and reported toxicity profile; and it has also, in some countries, been used in the HIPEC setting with 5-days of 5-FU EPIC. The initial plan was to do a direct phase III study. However, since it is planned to give a single dose of 5-FU instead of 5 daily treatments, it will probably be possible to increase the concentration of 5-FU EPIC. As such, the study committee opted to do a dose-titration study (phase I) including 15-30 patients to evaluate the possibility of using a slightly higher single dose 24-hour 5-FU. Instead of a phase II trial, an interim analysis after treatment of the first 140 patients in phase III was added to evaluate safety and aim for a phase III final comparison including 326 patients.

The rationale behind two investigational drugs (irinotecan and 5-FU) is that adding only one drug is not enough to provide a synergy that can produce a reasonable investigational clinical effect (see figure 1). The dose-titration of irinotecan to oxaliplatin HIPEC has already been performed [14]. Thus, the phase I part of the trial is investigating the addition of 5-FU EPIC in a dose-titration manner to oxaliplatin + irinotecan HIPEC. The phase III part of the trial requires both drugs to be added for efficacy reasons and it is not feasible clinically to have several trial arms. Since the triple drug combination has already been in use in France with cytoreductive surgery and the combination is well studied and in use in clinical routine medical oncology treatment for metastasized colorectal cancer, it is the synergy of all three drugs combined with cytoreductive surgery that is being studied in phase III. Hence, all conclusions will be related to the combination treatment as such.

The risks of adding 5-FU EPIC to HIPEC has been reviewed already in several trials [7]. The risk of morbidity, reoperation, or postop mortality is not increased [6]. Although, one particular side-effect of neutropenia is expected to increase, it does not increase the risk of other morbidity [8]. In order to offset this side-effect, a planned bone marrow stimulation treatment will be administered.

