# STUDY DESIGN

## Study outline

A dose titration study and a combined superiority registry-based open-label randomized control trial is planned to answer the trial objectives. The study will be registry-based to allow simpler and more comprehensive follow-up. Patients with colorectal cancer will be treated with cytoreductive surgery (CRS) together with either standard oxaliplatin HIPEC (the control for the efficacy study) or oxaliplatin/irinotecan HIPEC in combination with 5-FU 24-hour EPIC. The 5-FU will be administered postoperatively when the abdomen is completely sutured. The drug is divided equally into 2 injections of 200 ml each and injected through two abdominal drains that are clamped for 16hours.

For dose escalation, the titration groups (á 3 or 6 patients) are followed for 30 days postoperatively after which the Data Monitoring Committee (DMC) will determine whether or not to increase the 5-FU dose for the following group of patients.

To study efficacy, randomization is performed intraoperatively. The patient is followed up postoperatively for a total of 3 years for the secondary endpoints which may be extended by the study committee to 5 years. Since the trial is registry based, the long-term follow-up does not require separate eCRF evaluations. These evaluations can be automatically retrieved from the registry – both recurrence data, quality of life, and morbidity data. Some specific eCRF evaluations will be integrated as a separate study part of the HIPEC registry, such as inclusion/exclusion criteria and adverse event reporting (including SUSAR reporting).

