- Granulocyte colony stimulating factor given postoperative only as needed when the leukocyte count falls below normal range.

Arm B (HIPEC + EPIC) Experimental treatment (normal dose and 1 dose level reduction)

- Oxaliplatin – 360 mg/m^2^ (HIPEC) – 25% dose reduction 270 mg/m^2^
- Irinotecan – 360 mg/m^2^ (HIPEC) – 25% dose reduction 270 mg/m^2^
- 5-FU – 400 mg/m^2^ IV bolus (Intraop) - 25% dose reduction 300 mg/m^2^
- Calcium folinate – 60 mg/m^2^ IV (Intraop)
- 5-FU – 250-850 mg/m^2^ IP 24-hour dwell in 400ml of 9% saline solution (End of op) (25% dose reduction 190-640 mg/m^2^)
  - The EPIC treatment is only 1 day and is administered after the abdomen is completely sutured in the operating theatre. The dose will be divided equally into 2 injections á 200ml each through two abdominal drains. The drains may be flushed with 20ml saline solution so that the chemotherapy is not lingering in the drain catheter. Afterwards, all drains are clamped for 16 hours. They are then opened in order to drain the abdominal cavity postoperatively.
- Granulocyte colony stimulating factor (G-CSF – e.g. filgrastim 5µg/kg/day) administered prophylactically on postoperative day 4 to 8 (5 days). If the neutrophil count is under normal range after 5 days of prophylactic treatment, the treatment may continue until the count is normalized, as clinically indicated. If leucocytosis occurs, the prophylactic treatment can be terminated earlier than after 5 days.

G-CSF may be administered as needed before or after the prophylactic period if an early or late neutropenia is detected.

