## Determination of sample size

Dose titration study

15-30 patients depending on how many dose levels require 6 patients.

Interim trial safety evaluation

140 patients (70 in each arm) which is close to 50% of the sample size for an extended safety analysis. See 13.2.1.2.

Efficacy study

Using an alpha of 5% and beta of 80% and a 12-month recurrence free survival benefit from 50% till 66% from a recent retrospective study comparing Ox HIPEC vs Oxiri HIPEC for colorectal cancer (figure 1, [6]), 148 patients is needed in each arm. With 10% loss to follow up or violation rate, 163 patients in each arm will be needed. In total, 326 patients are to be included in the colorectal cancer group which will define the sample size.

In total, approximately 341-356 patients will be recruited for the phase I/III trial which will be included from 4 centers with the following estimations:

Uppsala – 114-118 patients

Stockholm – 114-118 patients

Malmö – 57-59 patients

Göteborg – 57-59 patients

Aarhus – patient count pending

Oslo – patient count pending

The CRS and HIPEC operation rate in Sweden is approximately 180 patients/year. Two-thirds are diagnosed with colorectal cancer leaving 120 potential candidates to be included in the study. If we manage a 90% inclusion rate, the dose titration part of the trial will take 6 months followed by another 4.5 years to study efficacy (see 20.5 for further details). The trial program will take approximately 5 years to complete.

##

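### Translational study: the sensitive-drug versus only-resistant-drugs grouping depends on randomized arm, and no adjustment for arm is named

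*Protocol*

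**What the plan says.** Protocol 11.1.1 (Translational study) sets out to learn whether ex vivo resistance testing predicts outcome. Two analyses are described.

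- **By assay value.** Resistance is defined by "top 1/3 of the whole study cohort’s IC_50_ values vs bottom 2/3", and "a Cox proportional hazards model will be implemented to evaluate whether the resistant oxaliplatin/irinotecan/5-FU values" lead to worse overall and recurrence-free survival.
- **By drugs received.** "Patients having received at least one sensitive drug during treatment will be compared to the patients having received only resistant drugs".

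The section lists no covariates and no stratification for either analysis. Tissue testing is done at Uppsala and is optional at the other three Swedish centres.

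The arms differ in what they receive. The synopsis gives the control as "Injection of oxaliplatin 460 mg/m^2^ and an intraoperational IV of 5-fluorouracil 400 mg/m^2^, and calcium folinate 60 mg/m^2". Section 8.1 (Study outline) contrasts "either standard oxaliplatin HIPEC (the control for the efficacy study) or oxaliplatin/irinotecan HIPEC in combination with 5-FU 24-hour EPIC". Section 10.1 (Treatment administration) lists irinotecan under arm B only: "Irinotecan – 360 mg/m^2^ (HIPEC) – 25% dose reduction 270 mg/m^2". Both arms receive the IV 5-FU bolus.

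**The concern.** A patient falls in the only-resistant group when every tested drug that he or she received is classed as resistant. The more drugs a patient receives, the less likely this is, even if the assay carries no information. Arm B patients receive three of the tested drugs and arm A patients two. Unless resistance is perfectly correlated between drugs, the only-resistant group is therefore enriched for arm A and the sensitive group for arm B.

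If arm B has better recurrence-free survival, as the trial hopes, part of that benefit appears in the pooled comparison as predictive value of the test. If arm B does worse, the distortion runs the other way. Section 5.4 says that "it is the synergy of all three drugs combined with cytoreductive surgery that is being studied in phase III", and a pooled comparison cannot separate the effect of that combination from what the assay adds. At stake is the interpretation of the translational result. The trial's main conclusion is not involved.

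**Working it through.** The protocol gives no sample size, power or expected effect for this comparison, so there is no figure of its own to reproduce. The treatment effect used below comes from section 13.3: "12-month recurrence free survival benefit from 50% till 66"%. That input does reproduce the stated 148 per arm (149 by the normal approximation, 148 by the arcsine formula).

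**Inputs**
- P(resistant) = 1/3 per drug, from the top-third cut-off (11.1.1).
- Tested drugs received: oxaliplatin and 5-FU in arm A; oxaliplatin, irinotecan and 5-FU in arm B (synopsis, 8.1, 10.1).
- Treatment hazard ratio (HR), assuming exponential times: ln 0.66 / ln 0.50 = 0.599. Section 16.3 also gives 0.81, used as an alternative.
- 1:1 allocation.
- Correlation of resistance between drugs: not given. Assumed 0, with 0.5 on a latent normal scale as a moderate case.

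**Step 1: group membership (independent resistance)**
- Arm A only resistant: (1/3)² = 11.1%
- Arm B only resistant: (1/3)³ = 3.7%
- Arm A share of the only-resistant group: 0.111 / (0.111 + 0.037) = 0.75
- Arm A share of the sensitive group: 0.889 / (0.889 + 0.963) = 0.48

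**Step 2: what an uninformative test would show**
- 12-month RFS, only resistant: 0.75 × 50% + 0.25 × 66% = 54.0%
- 12-month RFS, sensitive: 0.48 × 50% + 0.52 × 66% = 58.3%
- Spurious difference: 4.3 points
- Ratio of mean hazards, only resistant to sensitive: (0.75 + 0.25 × 0.599) / (0.48 + 0.52 × 0.599) = 1.14

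A large simulated Cox fit without arm (exponential times, censoring at 60 months) gives about 1.15.

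**Step 3: sensitivity to the assumptions.** The entries are the simulated Cox HR, only resistant versus sensitive, for a test with no information.

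| Treatment HR | Resistance between drugs | IV 5-FU counted in arm A | IV 5-FU not counted |
|---|---|---|---|
| 0.60 | independent | 1.15 | 1.29 |
| 0.60 | correlation 0.5 | 1.06-1.07 | 1.17 |
| 0.81 | independent | 1.06 | 1.11 |
| 0.81 | correlation 0.5 | 1.02-1.03 | 1.07 |
| 1.00 | either | 1.00 | 1.00 |

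At correlation 0.5 with IV 5-FU counted, about 18% of arm A and 12% of arm B are only resistant. If the IV bolus is not counted and resistance is independent, the figures are 33% and 4%.

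**Step 4: false-positive rate at a nominal 5%.** With 163 tested per arm and IV 5-FU counted, the unadjusted rate is about 6-12%. With 57 per arm, roughly what Uppsala alone could supply, it is about 5-9%. If arm A's IV 5-FU is disregarded, it is about 8-42% at 163 per arm.

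**Step 5: with arm in the model.** In every scenario the HR returns to about 1.00. At 163 per arm the false-positive rate returns to about 5% (5.1-5.5% in the simulated cases).

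**The case against.** - **Silence is not exclusion.** Section 11.1.1 gives no covariate list at all, and the adjustment set for an optional analysis is commonly left to the SAP. Where the protocol does list covariates for survival models (13.2.1), treatment arm comes first. This stands in part: a reader might infer that the plan leaves arm out on purpose, and the text does not support that. But the protocol itself fixes a grouping that depends on arm, so following the text as written would confound it.
- **The Cox model is tied to the IC50 split.** This stands. A reader might infer that the whole translational analysis is confounded. The top-third versus bottom-two-thirds analysis rests on assay values and not on drugs received, so it is not affected in this way. It also appears to cover the individual drugs already.
- **The bias is modest.** This stands. A reader might infer that a useless test would be declared predictive. With IV 5-FU counted, the spurious HR is about 1.03-1.15, and a small tested subset would often not detect it.
- **The largest figure requires ignoring arm A's 5-FU.** Arm A does receive 5-FU during surgery, so counting it is the more natural reading. The protocol does not say which administrations count, so 1.29 is an upper bound and not the expected case.
- **Low consequence.** The analysis is optional, is not among the stated objectives or endpoints, and feeds no trial decision. This stands and limits the weight of the point.

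**Conclusion.** The point holds for the drugs-received comparison only. Its two groups differ in arm composition by construction, and no adjustment for arm is named. With independent resistance, the planned 50% versus 66% effect and IV 5-FU counted in both arms, an uninformative test would show an HR of about 1.15. The figure is about 1.07 under moderate correlation, about 1.03-1.07 if the treatment HR is 0.81, and 1.00 if the arms do not differ or resistance is perfectly correlated. It reaches about 1.29 only if arm A's IV 5-FU is disregarded. These sizes rest on assumed correlations and exponential survival. The direction, given a benefit in arm B, follows from the protocol's own definitions. The primary endpoint is unaffected. The change is worth making but is not critical.

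**What to change.** In section 11.1.1, state that the comparison of the sensitive and only-resistant groups will use a Cox model stratified by randomized arm, or will be made within each arm and then pooled. State also whether IV bolus 5-FU counts as a drug received when the groups are formed. This costs one stratification term and one sentence of definition, with no new data. The only downside is a slight loss of precision, because the only-resistant group is small: about 24 of 326 patients under independence, 163 × (0.111 + 0.037), if all were tested.
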